### 510 **7.1.3 Mood outcomes**

511 Mood related outcomes will be evaluated by different self-report questionnaires and clinician-  
512 rated scale as detailed below (before the infusions at treatment visits). A trained clinician such as  
513 a psychiatrist or a research assistant with at least a master's degree, blinded to the patient  
514 assignment, will complete the clinician-rated questionnaires.

- 515 1. Change From Baseline in Montgomery-Asberg depression rating scale (MADRS) Total  
516 Score to Last Treatment [ Time Frame: Baseline, Week 4] 
- 517 2. Change From Baseline in MADRS Total Score to Follow-up [ Time Frame: Baseline, 1-  
518 month follow-up (8 weeks)] 
- 519 3. Change From Baseline in Beck Depression Inventory (BDI-II) Total Score to Last  
520 Treatment [ Time Frame: Baseline, Week 4] 
- 521 4. Change From Baseline in Beck Depression Inventory (BDI-II) Total Score to Follow-up  
522 [ Time Frame: Baseline, 1-month follow-up (8 weeks)] 
- 523 5. Change From Baseline in Clinician-Rated Global Impression Improvement Score to Last  
524 Treatment [ Time Frame: Baseline, Week 4] 
- 525 6. Change From Baseline in Clinician-Rated Global Impression Severity Score to Last  
526 Treatment [ Time Frame: Baseline, 1-month follow-up (8 weeks)] 

### 527 **7.1.4 Anxiety outcomes**

528 Anxiety related outcomes will be evaluated by self-report questionnaires as detailed below  
529 (before the infusions at treatment visits).

- 530 1. Change From Baseline in STAI-Y A to Last Treatment [ Time Frame: Baseline, Week 4]

531 

- 532 2. Change From Baseline in STAI-Y A to Follow-up [ Time Frame: Baseline, 1-month  
533 follow-up (8 weeks)]
- 534 3. Change From Baseline in STAI-Y B to Last Treatment [ Time Frame: Baseline, 1-month  
535 follow-up (8 weeks)]
- 536 4. Change From Baseline in STAI-Y B to Follow-up [ Time Frame: Baseline, 1-month  
537 follow-up (8 weeks) ]

### 538 **7.1.5 Suicidality outcomes**

539 Suicidality-related outcomes will be evaluated by different self-report questionnaires and  
540 clinician-rated scale as detailed below (before the infusions at treatment visits). A trained  
541 clinician such as a psychiatrist or a research assistant with at least a master's degree, blinded to  
542 the patient assignment, will complete the clinician-rated questionnaires.

- 543 1. Change From Baseline in Beck Scale for Suicide Ideation (SSI) Total to Last Treatment  
544 [ Time Frame: Baseline, Week 4] 
- 545 2. Change From Baseline in Beck Scale for Suicide Ideation (SSI) Total to Follow-up  
546 [ Time Frame: Baseline, 1-month follow-up (8 weeks)]
- 547 3. Change From Baseline in Clinician-Rated Global Impression Suicidality Severity Score  
548 to Last Treatment [ Time Frame: Baseline, Week 4] 
- 549 4. Change From Baseline in Clinician-Rated Global Impression Suicidality Improvement  
550 Score to Last Treatment [ Time Frame: Baseline, Week 4] 
- 551 5. Change From Baseline in Clinician-Rated Global Impression Suicidality Severity Score  
552 to Follow-up [ Time Frame: Baseline, 1-month follow-up (8 weeks)]
- 553 6. Change From Baseline in Clinician-Rated Global Impression Suicidality Improvement  
554 Score to Follow-up [ Time Frame: Baseline, 1-month follow-up (8 weeks)]

555  
556  
557  
558  
559  
560

### 7.1.6 Other

Psychological and physical pain, sleep and experience-related outcomes will be evaluated by different self-reported questionnaire as detailed below (before the infusions at treatment visits unless otherwise specified). Qualitative assessment of subjective experiences of patients undergoing ketamine therapy will be performed by semi-structured interviews lasting 1 to 2 hours and scheduled one or two weeks after all the dosing sessions. In addition, patient-clinician interactions, including the dosing period and the debriefing, will be recorded for each session.

1. Sleep: Change From Baseline in PSQI Total and Subscores to Last Treatment  
[ Time Frame: Baseline, Week 4] 
2. Sleep: Change From Baseline in PSQI Total and Subscores to Follow-up  
[ Time Frame: Baseline, 1-month follow-up (8 weeks)] 
3. Change From Baseline in Psychological and Physical Pain to Last Treatment  
[ Time Frame: Baseline, Week 4] 
4. Change From Baseline in Psychological and Physical Pain to Follow-up  
[ Time Frame: Baseline, 1-month follow-up (8 weeks)] 
5. The Mystical Experience Questionnaire (MEQ) after each treatment  
[ Time Frame: Immediately after the interventions] 
6. The Emotional Breakthrough Inventory (EBI) after each treatment  
[ Time Frame: Immediately after the interventions] 
7. The Psychedelic Music Questionnaire Short-Form (PMQ-SF) after each treatment  
[ Time Frame: Immediately after the interventions]
8. Qualitative assessment using interpretative phenomenological analysis (IPA) of patients subjective experiences based on semi-structured interviews conducted 1 to 2 week after completion of all dosing sessions, and by audio recordings of patient-clinician interactions during every dosing session

589

## 590 **7.2 Adverse events**

591 Information regarding the occurrence of potential adverse effects during/after ketamine sessions  
592 (e.g. headache, nausea and vomiting, neuropsychiatric symptoms, hypertensive peak, etc.) will be  
593 captured throughout the study in both groups.

## 594 **7.3 Evaluations by visit**

595 The following table lists the assessment procedures and indicates (X) in which visits they are  
596 performed. Written informed consent will be obtained before performing any procedure. The sites  
597 investigators are responsible for ensuring that all assessments are performed according to the  
598 protocol, and that data are recorded in the appropriate forms. Missed or partial visits/ assessments  
599 must be reported on the case report forms (reasons should be provided).

|                                      | Phase                   |              |               |           |
|--------------------------------------|-------------------------|--------------|---------------|-----------|
| Data collection                      | Screening & Preparation | Pre-infusion | Post infusion | Follow-up |
| Demographics                         | x                       |              |               |           |
| Medical and Psychiatric Hx           | x                       |              |               |           |
| Medication                           | x                       |              |               |           |
| Physical examination and BMI         | x                       |              |               |           |
| Informed consent form                | x                       |              |               |           |
| Inclusion / exclusion criteria       | x                       |              |               |           |
| Blood Pressure                       | x                       | x            | x             |           |
| Mood questionnaire (self-reported)   |                         | x            |               | x         |
| Mood questionnaire (clinician-rated) |                         | x            |               | x         |

|                                              |  |   |   |   |
|----------------------------------------------|--|---|---|---|
| Anxiety questionnaires (self-reported)       |  | x |   | x |
| Suicidality questionnaires (self-reported)   |  | x |   | x |
| Suicidality questionnaires (clinician-rated) |  | x |   | x |
| Sleep questionnaire (self reported)          |  | x |   | x |
| Psychological & Physical Pain questionnaires |  | x |   | x |
| Experiential questionnaires                  |  |   | x |   |
| Semi-structured interviews                   |  |   |   | x |

## 8. Statistical analysis

### 8.1 Sample size calculation

This study is a pilot trial. There is currently limited data to justify the sample size, given the innovative nature of studying music on hemodynamic tolerance during sub-anesthetic ketamine infusions. Furthermore, performing a priori power analyses with a within-subject factor is complicated and difficult to perform accurately without a prior study to justify correlations between levels and sphericity assumptions. This pilot RCT will thus provide the necessary and adequate data to plan a subsequent confirmatory RCT.

A preliminary power analysis was done to estimate the number of patients required for this study and computed a priori using the software G\*Power 3.1, University Düsseldorf, Germany. The sample size calculation was based on the results of Mok et al. who studied the impact of music on hemodynamic functioning in preoperative patients, given the similar within-between study design and procedure. They found pre-post differences of systolic blood pressure of  $-3,5 \pm 14.5$  mmHg in the music group and no changes ( $+0,1 \pm 10,3$  mmHg) in the control group. A two-sided 0.05

level of significance and a sample size of 28 patients (14 patients per group), each providing six pre-post datapoints, provided 80% statistical power to significantly demonstrate this difference in systolic blood pressure, assuming sphericity of 1 and correlations among measures of 0.5. To accommodate for a 10% attrition rate (given low attrition rate in ketamine trials for depression, we will recruit a total of 30 patients (G\*power 3.1, ANOVA Repeated measures, within between interaction), a feasible recruitment rate at the current clinical capacities over 12-18 months.

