## **8.3 Analysis of the primary outcome**

For the primary outcome data analysis, we will adopt the generalized linear model (GLM) to investigate the change in systolic blood pressure (SBP) at 40 minutes versus at 0 minutes between intervention and control groups. Specifically, we will treat the difference between the average of the triplicate SBP measurements at 0 minutes and 40 minutes at each infusion as the outcomes in the GLM, adjusting for covariates such as intervention, age and sex. The generalized estimating equation (GEE) technique is proposed to estimate the regression coefficients, and the corresponding variances are estimated by the sandwich estimators. GEE will be used to account for the clustering (non-independence) of the data attributed to the longitudinal and repeated measures design of this study. A Gaussian regression with an identity link for continuous outcomes will be used to estimate mean differences between treatment groups, fitted with robust error estimation and an ar1 working correlation structure. We will use Inverse-probability

weighting (IPW) to account for missing data and augmentation (AUG) for imbalance in  
covariates between treatment groups for doubly robust GEE estimation.

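### The 80% power claim does not follow from the plan's inputs: 28 patients give about 47% on the test named and about 16% for the between-arm SBP contrast that is analysed

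*Supplement*

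**What the plan says.** Section 8.1 calls the study a pilot and the power analysis preliminary. It takes its effect from a study of music in preoperative patients: an SBP change of -3.5 (SD 14.5) mmHg with music and +0.1 (SD 10.3) mmHg without. It states that a "sample size of 28 patients (14 patients per group), each providing six pre-post datapoints, provided 80% statistical power" for that difference, at two-sided 0.05, with sphericity 1 and a correlation of 0.5 among measures. The G*Power option is given as "ANOVA Repeated measures, within between interaction". The effect size f that was entered is not given. Thirty patients are to be recruited.

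Section 8.3 takes the 0-to-40-minute SBP change at each infusion as the outcome and fits a GEE with an AR(1) working correlation. The Gaussian model "will be used to estimate mean differences between treatment groups". No arm-by-infusion term is named. Section 2.1 states the central hypothesis that music significantly reduces the SBP rise, and section 5.1 defines the primary outcome as the 0-to-40-minute change compared between arms.

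**The concern.** There are two separate problems.

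1. The quoted means and SDs describe a small standardised effect. The 80% does not come out of them, even on the test that 8.1 names.
2. With six change scores per patient, the interaction test has 5 numerator degrees of freedom and asks whether the arm difference varies from infusion to infusion. Section 8.3 asks for the arm difference averaged over infusions. Correlation between infusions helps the first and hurts the second, so power for one says nothing reliable about the other.

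At stake is how the result will be read. A reader told that the trial has 80% power for 3.6 mmHg would take a null result as evidence against music, when the design would miss an effect of that size about five times in six (at correlation 0.5). Section 8.1 also says that the pilot will supply what is needed to plan a confirmatory trial. If that trial is sized by the same method, it will be far too small.

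**Working it through.** **Inputs, all from section 8.1:** changes -3.5 (SD 14.5) and +0.1 (SD 10.3) mmHg; N = 28, 14 per arm; m = 6 measures; correlation ρ = 0.5; sphericity 1; two-sided 0.05. The value of f is not stated. I assume f = d/2 with the pooled SD, which is the usual conversion for two equal groups.

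**Effect size**
- Difference = 0.1 - (-3.5) = 3.6 mmHg
- Pooled SD = √((14.5² + 10.3²)/2) = 12.58
- d = 3.6/12.58 = 0.286; f = 0.143; f² = 0.0205

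**The plan's own test (within-between interaction)**
- λ = f²·N·m/(1-ρ) = 0.0205 × 28 × 6/0.5 = 6.88
- df = (2-1)(6-1) = 5 and (28-2)(6-1) = 130
- Power = 47.4%, against the stated 80%. Reaching 80% takes 54 patients.

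With f = 0.20 the same formula gives 80.2% at N = 28 and 76.5% at N = 26. So 28 is the smallest balanced N for f = 0.20 with six measures. That f means 0.40 × 12.58 = 5.0 mmHg, not 3.6.

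Interaction power at N = 28 under other choices of SD and m:

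| SD used | m = 6 | m = 12 (0- and 40-minute values counted separately) |
|---|---|---|
| 14.5 | 36.0% | 52.3% |
| 12.58 (pooled) | 47.4% | 67.6% |
| 12.4 (plain mean of SDs) | 48.6% | 69.2% |
| 10.3 (control only) | 66.9% | 87.5% |

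None of these comes out at 80%. The only cell above it needs 12 measures and the smaller SD applied to both arms, against the quoted SDs and the six datapoints.

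**The contrast analysed in 8.3 (between arms, averaged over infusions)**
- λ = f²·N·m/(1+(m-1)ρ) = 0.0205 × 28 × 6/3.5 = 0.98
- df = 1 and 26
- Power = 15.9%

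The numerator f²·N·m = 3.44 is the same in both tests. The interaction divides it by 0.5 and the between-arm test by 3.5, so the noncentrality differs sevenfold.

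The same result on the scale of the patient mean: the SD of a six-infusion mean is 12.58 × √(3.5/6) = 9.61 mmHg. The difference detectable with 80% power is 10.6 mmHg at 14 per arm and 10.2 at 15 per arm. The expected 95% CI half-width at 15 per arm is 2.048 × 9.61 × √(2/15) = 7.2 mmHg.

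| Correlation between infusion changes | Power for 3.6 mmHg, 14 per arm | Difference detectable with 80% power, 14 per arm | Patients per arm for 80% at 3.6 mmHg |
|---|---|---|---|
| 0 | 43% | 5.6 mmHg | 33 |
| 0.3 | 20% | 8.9 mmHg | 81 |
| AR(1), 0.5 | 21% | 8.6 mmHg | 76 |
| 0.5 exchangeable | 16% | 10.6 mmHg | 113 |
| 0.7 | 13% | 12.0 mmHg | 145 |

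With all 30 patients analysed and exchangeable correlation 0.5, power is 16.8%. At SD 10.3 or 14.5 in place of 12.58 (14 per arm), it is 21.5% or 13.2%.

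**The case against.** The best case on the other side has three parts.

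**The inputs are ambiguous.** Section 8.1 does not say what the 0.5 correlates. If it applies to all twelve SBP readings in a patient, the covariance of changes from two infusions is 0.5 - 0.5 - 0.5 + 0.5 = 0, and between-arm power is 43%, with 5.6 mmHg detectable. If it is AR(1), as in the working structure of 8.3, power is about 21%. Likewise f and the number of measures are not given, so 47% depends on f = d/2, the pooled SD and m = 6. This stands in part: the 16% and the 113 per arm are conditional and should carry their range. But the whole range lies far below 80%, and the exact match of N = 28 with f = 0.20 at m = 6 points to six measures having been entered.

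**The interaction might be the endpoint.** If before and after were entered as a two-level factor, the arm-by-time interaction is the difference in change. That is right in principle, but with two levels the same inputs give 31% power, and 8.1 refers to six datapoints per patient.

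**It is a pilot, and 8.1 says the data are limited.** This is true, and it is why no larger sample is asked for. A pilot may have low power, but 8.1 still asserts that the sample "provided 80% statistical power to significantly demonstrate this difference in systolic blood pressure", and section 2.1 sets a hypothesis of a significant reduction.

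Adjustment for age and sex is not credited above. To reach 80% for 3.6 mmHg at correlation 0.5, it would have to cut the SD from 12.58 to about 4.3, a third of its value, which is not plausible.

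**Conclusion.** The concern holds. From the figures quoted in 8.1, power on the named test is about 47%, not 80%, assuming f = d/2, pooled SD and six measures. For the contrast that 8.3 estimates, it is about 16% at exchangeable correlation 0.5, and from 13% to 43% as that correlation runs from 0.7 down to 0. The design has 80% power for about 10.6 mmHg at correlation 0.5, nearly three times the 3.6 mmHg assumed. The mismatch between the powered test and the analysed contrast does not depend on which f was entered. The claim must be corrected because it concerns the primary outcome and is wrong as written.

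**What to change.** Keep 30 patients and rewrite section 8.1:

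- Withdraw the 80% statement and the interaction option.
- State the f, SD, number of measures and correlation used, and say that the correlation is between infusion-level changes.
- Report for the averaged between-arm change: about 16-17% power for 3.6 mmHg with 28-30 patients, 80% power for about 10.2-10.6 mmHg, and an expected 95% CI half-width of about ±7 mmHg, all at correlation 0.5. Show the range over other correlations.
- Preferably, name the pilot goal in 8.1 and section 2.1 as estimating the effect with its CI, together with the SD and the between-infusion correlation needed for the confirmatory trial. It would also help to say that a non-significant result is not evidence of no effect.

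The cost is wording and a less favourable stated power. No patients, visits or analyses change.

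### Recruiting 30 patients covers about 6.7% attrition from the required 28, not the 10% stated (minor arithmetic error)

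*Supplement*

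**What the plan says.** Section 8.1 (Sample size calculation) bases the size on a preliminary G*Power calculation for a repeated-measures ANOVA, testing the within-between interaction at a two-sided 0.05 level. It reports that "a sample size of 28 patients (14 patients per group), each providing six pre-post datapoints", "provided 80% statistical power", "assuming sphericity of 1 and correlations among measures of 0.5". It then turns to dropout: to "accommodate for a 10% attrition rate", the protocol says, "we will recruit a total of 30 patients".

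The Protocol Summary, Section 3 (Study Design) and Section 4.4 (Randomization Process) all repeat 30 patients, the Summary and Section 4.4 as 15 per arm. The protocol gives no other attrition rate, no rule for replacing patients who leave, and no larger target.

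**The concern.** An attrition allowance is meant to leave the required number of patients after the expected loss. Here the required number is 28 and the expected loss is 10%, and 30 does not leave 28. Any reader can see this with one multiplication.

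What is at stake is the accuracy of the statement that 10% attrition is covered. Section 8.1 also says that this pilot is to supply the data for planning a confirmatory trial, so an allowance calculated this way could be carried forward.

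**Working it through.** **Inputs, all from Section 8.1 unless noted.** Required patients 28 (14 per arm); six change scores per patient (m = 6); power 80%; alpha 0.05; correlation rho = 0.5; sphericity epsilon = 1; attrition 10%; recruitment 30; allocation 1:1 (Section 4.4).

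**1. Trying to reproduce the 30.**
- Standard inflation, N/(1 − d): 28/0.90 = 31.1, so 32 with equal arms.
- Common shortcut, N × (1 + d): 28 × 1.10 = 30.8, which rounds up to 31. Only rounding down gives 30.

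**2. What 30 delivers.**
- Expected to remain after 10% loss: 30 × 0.90 = 27, or 13.5 per arm against 14.
- Largest loss that still leaves 28: (30 − 28)/30 = 2/30 = 6.7%.
- For comparison: 31 × 0.90 = 27.9 and 32 × 0.90 = 28.8.
- Assuming that each patient leaves independently with probability 10%, the binomial chance of keeping at least 28 is about 41% from 30 recruited and 79% from 32.

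**3. What one patient costs in power.** For the named model with k = 2 groups:
- noncentrality lambda = f² × N × m × epsilon/(1 − rho)
- df1 = (k − 1)(m − 1) × epsilon
- df2 = (N − k)(m − 1) × epsilon

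The documents do not state f. Solving for the f that gives exactly 80% at N = 28 returns f = 0.1996. The rounded value f = 0.20 is shown beside it.

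| N | df1, df2 | lambda at f = 0.20 | Power, f = 0.20 | Power, f = 0.1996 |
|---|---|---|---|---|
| 28 | 5, 130 | 0.04 × 28 × 6/0.5 = 13.44 | 80.2% | 80.0% |
| 27 | 5, 125 | 0.04 × 27 × 6/0.5 = 12.96 | 78.4% | 78.2% |

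The loss is about 1.8 percentage points on either value. The formula treats all 27 patients as complete and anyone who left as contributing nothing.

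**The case against.** The strongest reply is that the slip has almost no consequence, and much of that stands. The shortfall is one patient and under 2 points of power. Section 8.1 calls the trial a pilot and the power analysis preliminary, and it admits that such calculations are hard to do accurately without prior data. An uncertainty of one patient is well inside that.

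The second reply is that counting complete patients overstates the loss. Section 8.2 specifies intention to treat. Section 8.3 fits a GEE to the change score at each infusion, with inverse-probability weighting for missing data. A patient who leaves after three infusions still supplies three outcomes. By count alone, 28 complete patients give 28 × 6 = 168 change scores and 27 give 27 × 6 = 162, so three early leavers averaging two infusions each would make up the difference. A count is not the same as power, and a patient who leaves before the first infusion adds nothing, but 27 is clearly the worst case. Neither reply makes the sentence true: the 28 was calculated with six datapoints from every patient, and Section 8.1 does not invoke partial data to justify 30.

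Two stronger readings are tempting. A reader might infer that the 80% power claim fails because of the attrition error. The documents do not support that: the 80% is attached to 28 patients, before attrition is mentioned. A reader might also infer that the trial is materially underpowered for this reason, or must recruit 32. A loss of about 2 points in a self-described pilot whose primary analysis keeps partial data does not support that either. Whether 28 follows from the means and standard deviations quoted in Section 8.1 is a separate question, not decided here.

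**Conclusion.** The point holds as a minor arithmetic error. On the plan's own figures, 30 recruited patients allow for a loss of about 6.7% rather than 10%, and nothing elsewhere in the protocol repairs this. That part rests on no assumption beyond the stated 28, 10% and 30.

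The power figure of about 78% rests on three assumptions: that the stated 28 and 80% are correct, that f is the back-solved value of about 0.20, and that patients who leave contribute no data. The last is pessimistic for the primary outcome. The design, endpoint and analysis are unaffected.

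**What to change.** Keep the target of 30 and correct the sentence in Section 8.1 in one of two ways:

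- state that thirty patients allow for about 6.7% attrition (two patients); or
- keep the 10% rate and state that 27 complete patients are then expected, with about 78% power on the plan's own assumptions.

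Either version should add that, under the GEE analysis in Section 8.3, patients who leave early still contribute their available infusions. If the second version is used, the sponsor should take the power figure from its own G*Power input and give the f that was entered, since the 78% here comes from a back-solved value.

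The cost is one or two sentences and a slightly less favourable figure. Recruitment and analysis do not change.
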